### Intervention

The intervention will consist of the MBSR training developed by Kabat-Zinn [22] which consists of 8 weekly group (6–15 persons) sessions with a duration of 120 min each. In the 6th week, an additional session of practice in silence with a duration of 6 h will be included. The intervention consists of three primary components: (1) formal and informal meditation exercises, such as sitting meditation and yoga, (2) dialogue and (3) psychoeducation about stress and stress responses. A folder will be provided with information about each week’s session. Participants will be asked to practice daily for at least 35 min.

### Mindfulness teacher

The MBSR will be given by a mindfulness teacher who meets the criteria of the Association of Mindfulness Based Teachers in the Netherlands and Flanders and the internationally agreed good practice guidelines of the UK network for Mindfulness-Based Teachers mindfulnessteachersuk.org, 2015). If the trainer notes that a participant might be in need of additional mental support or if a participant indicates this him- or herself, a licensed psychologist is available who can be contacted during as well as after the programme.

### Sample size calculation

In determining the necessary number of participants, we have presumed a significance level (α) of 0.05 and a moderate effect size (δ) of 0.50 (e.g. Verweij et al, 2016). To achieve a power of 80%, we will need to include 64 participants in the intervention as well as the control group. With an estimated 17.5% drop-out, which is comparable to a similar study by Verweij et al, (2016), we will strive to recruit 155 participants divided over three school years.

### Data analysis

All analyses will be performed in R (R [23]) by an independent statistician who is further not involved in the project. The results will be reported in accordance with the extended CONSORT statement [24]. Descriptive statistics will be calculated for all variables of interest.

#### Effectiveness

The primary analyses will be based on the intention-to-treat principle and linear mixed models (LMMs) will be used for the primary analyses. LMMs adequately deal with missing data at random and can be used to account for the hierarchical structure of the data (i.e. multiple assessments nested within teachers, teachers nested within groups and schools). Time, condition and time by condition interactions will be specified as fixed factors to examine the effect of the intervention over time on primary and secondary continues outcomes. Baseline scores of the corresponding outcome will additionally be entered in the model to account for baseline imbalances. In accordance with the CONSORT statement, we will not statistically test whether the two groups differ in baseline variables. Therefore, the models that we will primarily report will not be adjusted for additional covariates. However, to examine whether adjusting the model for additional covariates substantially changes conclusions drawn from the analyses, we will conduct sensitivity analyses with the models adjusted for the following potentially confounding baseline variables: sex, age, school weight, teachers’ years of experience, number of work days per week and past or present psychological problems. All models will also be run with completers only as additional sensitivity analysis. Post hoc tests will be conducted for between-group differences at each timepoint using analyses of covariance (ANCOVA), including baseline scores of the corresponding outcome as covariate. Estimated marginal means and corresponding standard errors from the primary LMMs will be used to additionally calculate between-group effect sizes at each timepoint. Effect sizes will be expressed as Cohen’s *d* with 95% confidence intervals. In addition, a clinically significant change will be examined using the reliable change index [25].

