**Aim:**

In the current paper, we describe the protocol for a randomized controlled study (RCT) comparing an 8-week mindfulness-based stress reduction (MBSR) intervention with a wait list control condition in primary school teachers. We hypothesize that teachers who participate in the MBSR programme will report less stress (primary outcome) than those in the control group at post-test and at 3-month follow-up. We also expect a decrease in teachers’ absenteeism and improvements of mental health, teacher skills, classroom climate quality and the pupil-teacher relationship (secondary outcomes). Finally, we hypothesize that self-compassion, mindfulness skills and emotion regulation skills could mediate effects.

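### The timepoint differences named in the primary hypothesis are tested by separate ANCOVAs rather than by contrasts from the primary mixed model

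*Protocol article*

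**What the plan says.** The Aim paragraph of the abstract puts the primary hypothesis as a comparison at two timepoints: teachers in the programme "will report less stress (primary outcome) than those in the control group at post-test and at 3-month follow-up".

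Under Data analysis, Effectiveness, the primary analysis is an LMM under intention to treat. Its fixed effects are time, condition and their interaction, with the baseline score added. The reason given for the model is that "LMMs adequately deal with missing data at random and can be used to account for the hierarchical structure of the data", and the section lists assessments within teachers and teachers within groups and schools.

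The same paragraph assigns the test at each timepoint to another model: "Post hoc tests will be conducted for between-group differences at each timepoint using analyses of covariance (ANCOVA"). The baseline score is the only covariate named. The LMM's marginal means and standard errors are used for Cohen's d with 95% confidence intervals at each timepoint.

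The sample size section rests on one comparison: "we have presumed a significance level (α) of 0.05" and "a moderate effect size (δ) of 0.50", so that "we will need to include 64 participants in the intervention as well as the control group". No primary timepoint, testing order or success rule over the two timepoints is stated.

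**The concern.** The article names two properties that justify the LMM, then uses a method with neither property for the comparisons that the hypothesis describes. An ANCOVA at a single timepoint, in its standard form, leaves out teachers without that outcome and treats all teachers as independent. The reader of the trial report would then see, for the same comparison, an effect size and interval from one model and a p-value from another, based on different samples and variance structures. The two can disagree, for instance an interval that includes zero beside a p-value below 0.05.

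Course groups are the more serious part. MBSR teachers are taught together, while controls receive no programme before follow-up. Positive correlation within course groups makes the ANCOVA standard error too small. Schools are less of a worry here, because teachers are randomised individually and both arms can draw on the same school.

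A secondary issue is that two timepoints carry the hypothesis while the trial is sized for one test at 0.05.

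**Working it through.** **1. The plan's own figure.** Inputs from the sample size section: α = 0.05 (two-sided reproduces the result), δ = 0.50, power 80%, drop-out 17.5%.

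- Normal approximation: n per arm = 2 × (1.960 + 0.842)² / 0.50² = 62.8, so 63.
- Two-sample t-test: 63.77, so 64, with power 0.801.
- Drop-out: 128 / 0.825 = 155.15, against the stated 155.

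The figure reproduces. It covers one comparison at 0.05.

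**2. Course-group clustering, simple formula.** The Intervention section gives groups of 6 to 15. I assume six groups among 64 MBSR teachers, so m = 64/6 = 10.67. The ICC is not in the article, so 0.02 to 0.10 is my assumption. Clustering affects one arm only:

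- ratio of true to assumed standard error = √[(2 + (m − 1) × ICC) / 2]
- type I error = 2 × [1 − Φ(1.96 / ratio)]

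| ICC | ratio | type I error of one test |
|---|---|---|
| 0.02 | √1.097 = 1.047 | 6.1% |
| 0.05 | √1.242 = 1.114 | 7.9% |
| 0.10 | √1.483 = 1.218 | 10.8% |

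**3. Effect of baseline adjustment.** The formula ignores the covariate. Adjusting for baseline removes variance between teachers but not the group effect, so the residual ICC rises. With an assumed baseline correlation of 0.6 and ICC 0.05, the residual ICC is 0.05 / (0.05 + 0.95 × 0.64) = 0.076. The formula then gives ratio √[(2 + 9.67 × 0.076)/2] = 1.169 and a type I error of 9.4%.

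A simulation of null trials agrees (20,000 per setting, 64 per arm, ordinary ANCOVA, same correlation). At ICC 0.05 and groups of about 10 it gives 9.4% at post-test and 9.8% at follow-up. At post-test, groups of 6 give 7.2% and groups of 15 give 11.8%. At ICC 0 the error is 4.9% to 5.2%, as it should be.

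**4. Missing outcomes.** I read the LMM as modelling post-test and follow-up scores with baseline as covariate.

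- Seen at both follow-ups: used by the LMM and by both ANCOVAs.
- Seen at neither: contributes essentially nothing to the treatment contrast in either method.
- Seen at one only: used by one ANCOVA, while the LMM also draws on that score for the other timepoint.

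Only the third set is handled differently, and the article does not say how large it is. Losing these teachers costs precision and may bias the estimate if drop-out depends on more than arm and baseline. It does not by itself raise type I error.

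**5. Two timepoints, each at 0.05, no clustering.** The correlation between the two test statistics is assumed. The rows are bivariate-normal probabilities with no true effect at either timepoint; the last is simulated.

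| Success rule | r = 0.5 | r = 0.6 | r = 0.7 |
|---|---|---|---|
| Either timepoint | 9.07% | 8.75% | 8.35% |
| Both timepoints | 0.93% | 1.25% | 1.65% |
| Either, after a significant 2-df joint test | 4.17% | 3.99% | 3.78% |

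**The case against.** The strongest reply is that the LMM is declared primary and the ANCOVAs are labelled post hoc. A reader might infer from the hypothesis wording that the ANCOVAs are the real primary test. The article does not say so, and I do not claim it. It also plans LMM effect sizes with intervals at each timepoint, so most of the better analysis is already there. What remains is that the only significance test named for each timepoint comes from the weaker method, so the label does not settle the mismatch.

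A reader might also conclude that type I error exceeds 5% outright. The documents do not support that. The clustering part needs a positive ICC, which is not given. The multiplicity part arises only if success at either timepoint counts. The hypothesis joins the timepoints with an 'and', and post hoc may mean that the tests follow a joint test; under either reading there is no inflation.

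Nor does the drop-out figure measure what the ANCOVAs lose relative to the LMM. The 64 per arm already allows for it, and teachers with no follow-up score inform neither method.

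Finally, the article does not spell out how the ANCOVAs treat missing outcomes or course groups. Complete cases and no group term are the usual form of the method, not quoted features. An unseen analysis plan could add detail, but the article itself fixes ANCOVA as the method, so this is not merely an omission.

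**Conclusion.** The point holds as an inconsistency in the choice of analysis that should be fixed; it is not a fault that invalidates the trial. The per-timepoint p-values are to come from a model without the two properties for which the primary model was chosen, and they can disagree with the effect sizes beside them.

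The size depends on an ICC that the article does not give. With about six course groups and an ICC of 0.02 to 0.10, one ANCOVA has a type I error of roughly 6% to 11% by the simple formula. Baseline adjustment raises this somewhat, to about 9% at ICC 0.05. If the ICC is zero, clustering adds nothing.

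Multiplicity is secondary and conditional: about 8% to 9% under an uncontrolled either-timepoint rule at correlation 0.5 to 0.7, and no inflation if both timepoints are required. The article leaves open which rule applies.

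**What to change.** Replace the ANCOVAs with condition contrasts at post-test and at follow-up from the primary LMM, with group and school random effects and all available data. With post-test as the reference time, the post-test contrast is the condition term and the follow-up contrast is the condition term plus the interaction. Report the estimate, interval and p-value from that one model. The course-group effect should apply to the MBSR arm only, since controls attend no course before follow-up.

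State the success rule. Requiring both timepoints needs no correction. If either one suffices, control the error, for example by a fixed sequence (post-test at 0.05, then follow-up at 0.05 only if the first is significant) or by a joint test first. The fixed sequence is one acceptable choice among several. A Bonferroni split is also valid but costs more: 64 per arm would then give 71% power, and 80% would need 78 per arm.

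Apart from that last option, the cost is a change of analysis wording: no new data, no larger sample, and contrasts from a model that will be fitted anyway.

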#### Moderation and mediation

To get more insight in for whom the MBSR programme works best, we will test moderating effects of school weight, age, past or present psychological problems and teachers’ years of experience by testing interactions with condition. In addition, we will test possible mediating variables between condition and the outcomes. The analyses regarding potential moderators and mediators are exploratory since the power for the trial is calculated to establish evidence for main effects on the primary outcome variables. For the mediation analysis, we will follow the recommendations of Preacher and Hayes for mediation analyses [26, 27]. In the mediation models, *X* will be the categorical group variable (0=control, 1=intervention), *Y* will be the observed scores of primary or secondary continuous outcomes at post-test or follow-up and *M* will be the potential mediators, including self-compassion, mindfulness-skills and emotion-regulation skills. Total, direct and (specific) indirect effects will be calculated for all models. To decide whether effects are significant, corresponding 95% bias-corrected and accelerated confidence intervals will be calculated based on 5000 bootstrap samples [26, 28]. Separate simple mediation analyses will be run for each putative mediator. In addition, multiple mediation analyses will be conducted with all potential mediators included.

### Data collection

As soon as the participant is enrolled, across all assessments, he or she will only be identifiable via a unique pseudocode identifier to anonymize all data. A separate protected database will link the unique pseudocode to the participants’ names. Anonymous and non-anonymous (e.g. informed consent forms) data will be stored in separate password-protected folders. Questionnaire data will be collected and stored with the online electronic data capture software CASTOR EDC [29]], which tracks and logs any manual changes made to raw data. When questionnaires are not completed within the expected period, teachers will be sent online reminders. If no response follows, they will be contacted per telephone to discuss the absence of response and to motivate them to complete the questionnaires. In case participation is discontinued, reasons will be noted. Also, the number of sessions attended by each participant will be noted and sessions will be recorded. An overview of all measurements is given in Table 1.

**Table 1 Tab1:** Planning of measurements

Study period: June 2019 to August 2022				
Enrolment 3 consecutive school years June 2019–August 2021	Baseline assessment	Post-treatment assessment	3 months’ follow-up assessment	End of school year
Cohort 1 Cohort 2 Cohort 3	Sept 2019 Sept 2020 Sept 2021	Nov 2019 Nov 2020 Nov 2021	March 2020 March 2021 March 2022	July 2020 July 2021 July 2022
**Variable**				
*Primary:*				
Perceived Stress	x	x	x	
*Secondary:*				
Absenteeism	x			x
Mental Health	x	x	x	
Teacher skills	x	x	x	
Pupil-teacher relationship	x	x	x	
*Possible mediators:*				
Self-compassion	x	x	x	
Mindfulness skills	x	x	x	
Emotion regulation skills	x	x	x	

#### Data management plan

*Radboud University and its research institutes have set strict conditions for the management of research data.* The data management plan is a protocol for researchers, developed by the Radboud University and approved by important scientific funding agencies in the Netherlands. It is based on the general policy about Research Data Management, which was adopted by the executive board of the Radboud University in November 2013.

The data management plan contains detailed information about our research project, the organizational context, data management roles, costs, data collection process, overview of the research data, informed consent, ethics committee, privacy in the data collection phase, security in the data collection phase, storing during research, privacy in the processing / analysing phase, structuring and documenting data, sharing data during research, long-term storage, metadata and communication and access to the data. This data management plan is a dynamic document, which will be regularly updated based on discussion with colleagues and supervisors.

The data management protocol for this research was written in consultation with the Research Data Officer of the Behavioural Science Institute. Together with the support service for issues concerning the management of research data (the Expert Center Research Data of the Radboud University; http://www.ru.nl/rdm), the research data officer will help to store, share and reuse research data according to university’s policy. The support service and the data officer are independent from this study’s sponsor and there is no conflict of interest.

### Primary outcome measure

#### Perceived stress

Perceived Stress Scale [30]: This questionnaire (PSS) measures the global stress levels in the past month using questions about the degree in which life is perceived as unpredictable, uncontrollable and overburdening. This self-report questionnaire has 10 items, which are scored on a 5-point Likert scale. The Dutch version of this instrument has a good internal reliability with Cronbach’s *α* coefficients varying between .84 and .86 [31].

### Secondary outcome measures

#### Absenteeism

Teachers are asked about their absenteeism of the past year between the first and last day of the schoolyear (how many days they called in ill and with which frequency). In addition, teachers are requested to record their absence and frequency in the current year. To support this data, their records will be verified with the schools’ absence system.

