### Aims of the trial

The primary aim of this study is to investigate the effectiveness of MBSR in contrast to a wait list control condition in reducing perceived stress in teachers in primary education. The secondary aim is to examine the effects of the MBSR on (a) absenteeism of teachers, (b) teachers’ mental health, (c) teacher skills and (d) teachers’ experienced classroom climate and pupil-teacher relationship.

The third aim is to examine possible mediating factors of treatment outcome, such as mindfulness skills (i.e. observing, describing, acting with awareness, non-judgement and non-reactivity), self-compassion and emotion regulation skills. Based on research by Jennings [2], Roeser [18], Roeser et al. [19] and Skinner and Beers [20], we hypothesize that an improvement of mindfulness skills, self-compassion and emotion regulation skills will lead to a reduction of perceived stress. In addition, we explore whether school weight, age, past and present psychological problems and teachers’ years of experience act as potential moderators of programme effects. The final aim is to conduct qualitative interviews after the MBSR programme to get a more in-depth view of teachers’ perception of the impact of MBSR on their teacher skills, classroom climate and pupil-teacher relationship.

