## Methods/design

### Study design

The design of the study is a superiority RCT in which primary education teachers are randomly allocated with a ratio of 1:1to either the MBSR programme or the waiting list control condition (see Fig. 1). Because of practical and financial constraints, the control condition consists of no intervention. As we would like to offer MBSR to all the teachers who express interest, we also wanted to be able to offer it to those allocated to the control condition. The study protocol has been ethically approved by the Internal Review Board (IRB) of the [masked for blind review] and is registered under number ECSW-2019-029.

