#### Eligibility criteria

We will include teachers who meet the following criteria: (a) teaching at least two days in the same group during a school year between the start of the school year and March, (b) willing to fill out questionnaires in Dutch three times in a school year and (c) able to start the programme in either September or March.

Exclusion criteria will be previous participation in a Mindfulness-Based Cognitive Therapy, MBSR programme or a mindfulness-based workshop of more than 3-h duration. During the trial, there will be no restrictions with regard to concomitant interventions. However, participants will be requested to not participate in an MBSR course offered elsewhere if they are allocated to the wait list control condition.

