### Procedure and allocation

Recruitment will take place in a large urban area in the Netherlands. School boards in the study area will be informed about the study and asked to make their teachers aware of it. Teachers will also be recruited by social media and by presentations at schools. Interested teachers will receive an information leaflet and be invited for a screening interview by telephone. Teachers who are willing to participate will provide written informed consent which will be obtained by one of the researchers ([name]).

Participants will receive online questionnaires, which will be processed anonymously. Questionnaires will be administered before and after the MBSR or wait list period (September and November), and at 3 months’ follow-up (March). As participants will be aware whether they have or have not participated in the course by the time they complete the follow-up assessments, they cannot be kept completely blinded. We will compare data related to teacher absenteeism from the school year prior to that in which they participate in the research. After completion of the follow-up, teachers of the control group will be offered the MBSR programme as well. To include the required 155 participants, the intervention procedure between September and June will be repeated for three consecutive school years.

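### The absenteeism count runs to July, past the March point at which the wait-list arm is offered MBSR, so its last months no longer compare MBSR with no intervention

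*Protocol article*

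**What the plan says.** All references are to the protocol article.

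- **Aim** (Aims of the trial): "The secondary aim is to examine the effects of the MBSR on (a) absenteeism of teachers".
- **Comparator** (Study design): participants are "randomly allocated with a ratio of 1:1to either the MBSR programme or the waiting list control condition", and "the control condition consists of no intervention".
- **Outcome** (Secondary outcome measures, Absenteeism): for the year before the trial, "Teachers are asked about their absenteeism of the past year between the first and last day of the schoolyear". For the trial year, "In addition, teachers are requested to record their absence and frequency in the current year". The entries are to be checked against the schools' absence system.
- **Timing** (Data collection, Table 1): the absenteeism row is marked at baseline and in the end-of-school-year column, dated "July 2020 July 2021 July 2022". It is not marked in November or March. Every other listed outcome is marked at baseline, November and March.
- **Control arm** (Procedure and allocation): "After completion of the follow-up, teachers of the control group will be offered the MBSR programme as well". The same section runs the whole intervention cycle from September to June within one school year. Under Eligibility criteria, participants must be "able to start the programme in either September or March".

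**The concern.** Every questionnaire outcome stops at the March follow-up, before the wait-list arm is offered the course. Absenteeism is the one outcome whose measurement continues beyond that point. If the plan is followed as written, the trial-year total for a control teacher who accepts the offer adds a period without MBSR to a period during or after MBSR.

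Two things are at stake. The first is what the estimate means: a full-year difference does not answer the question in secondary aim (a) against the comparator named under Study design. The second is dilution: if MBSR lowers absence within the March to July months, the arms move closer together. A small observed difference could then reflect a weak effect, or an effect present in both arms late in the year, and the total could not tell these apart.

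**Working it through.** **1. The plan's own figures.** No figure is given for absenteeism. The sample size belongs to perceived stress and reproduces. A two-sample t-test with d = 0.50, two-sided alpha 0.05 (sidedness assumed) and 80% power needs 63.77, so 64 per arm. Allowing for 17.5% drop-out, 128/0.825 = 155.15, against the stated 155. Nothing below changes it.

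**2. The calendar.**

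| Period | MBSR arm | Wait-list arm | In the absenteeism count? |
|---|---|---|---|
| September to November | in the course | no intervention | yes |
| November to March | course completed | no intervention | yes |
| March to July | course completed | MBSR offered | yes |

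Only the last row departs from the stated comparator.

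**3. How much of the year this is.** Assume a school year of 10-11 months from September and a control start at month 6-7. The share of the counted year after the control start runs from (10-7)/10 = 30% to (11-6)/11 = 45%.

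**4. Illustrative dilution, ratio scale.** Every input here is an assumption: a 45-week year, the MBSR arm finishing at week 10, the control arm starting at week 27, an absence ratio of 0.70 once MBSR acts, and full uptake by controls.

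*Effect from the first session.*
- MBSR arm: 0.70.
- Control arm: (27 + 18 × 0.70)/45 = 0.880.
- Full-year ratio: 0.70/0.880 = 0.795. Without the delayed course it would be 0.70.
- Log effect kept: ln 0.795/ln 0.70 = 0.64, so 36% is lost, all of it to the delayed course.

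*Effect only after the course (controls trained by week 36.5).*
- MBSR arm: (10 + 35 × 0.70)/45 = 0.767.
- Control arm: (36.5 + 8.5 × 0.70)/45 = 0.943.
- Full-year ratio: 0.767/0.943 = 0.813. Without the delayed course it would be 0.767.
- Log effect kept: ln 0.813/ln 0.767 = 0.78, so 22% is lost to the delayed course.

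*At 50% uptake*, the average ratio in controls once MBSR acts is 0.85.
- From the first session: control (27 + 18 × 0.85)/45 = 0.940; ratio 0.745; loss 17%.
- After the course: control (36.5 + 8.5 × 0.85)/45 = 0.972; ratio 0.789; loss 11%.

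**5. Second illustration, additive scale.** Take a constant monthly effect, full uptake and the calendar of step 3. The retained share is (active months in MBSR arm − active months in control arm)/(active months in MBSR arm).
- From the first session: (11 − 5)/11 = 55% to (10 − 3)/10 = 70%.
- After a two-month course: (9 − 3)/9 = 67% to (8 − 1)/8 = 88%.

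The loss is therefore 12-45%, in the same region as step 4.

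**6. What ending in March does.** From September to week 27 no MBSR is planned in the control arm. The ratio is 0.70 if the effect starts with the course. If it starts after the course, the ratio is (10 + 17 × 0.70)/27 = 0.811, against 0.813 for the full year. In that second case the shorter window gives almost the same ratio from fewer absence days. What it restores is the comparator.

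**The case against.** **July may be only the collection date.** The outcome text says current year and gives no end date, and an analysis plan not shown could cut the count in March. This has some force. But the prior-year count is defined from the first to the last day of the school year, Table 1 puts the trial-year assessment at the end of that year, and no cut is stated. The protocol fixes both the July assessment and the March offer, so the conflict is in its text.

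**Stronger readings that a reader might infer.** Four of them go too far.

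- *That the only comparison is pre-post.* Procedure and allocation mentions a comparison with the prior school year. Table 1, however, makes prior-year absence the baseline value, and the Effectiveness section enters baseline scores in a model with condition. If absence is analysed that way, prior-year absence is a covariate in a randomised comparison.
- *That the delayed course costs up to 42% of the effect.* In the effect-after-course case, ln 0.813/ln 0.70 = 0.58, so 42% of the log effect is missing against 0.70. Of this, 26 points (1 − ln 0.767/ln 0.70) come from counting September to November. Counting from programme start is ordinary intention-to-treat practice and no error.
- *That a November to March count is clearly more powerful.* Take negative-binomial spells with an annual mean of 1.0-1.5, dispersion 0.5-1.0 and 64 per arm, all assumed. Power is then about 17-24% for November to March and 12-20% for the full year at full uptake. At 50% uptake with the effect from course start, the full year gives 20-30% and the order reverses. A September to March count gives 11-15% or 21-32%, depending on when the effect starts. Power is low throughout and does not settle the window.
- *That the full-year comparison is invalid.* It remains a randomised comparison of early with delayed MBSR. The difficulty is that the protocol does not describe it as one.

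It is also fair that the offer need not be accepted, and that dilution works against a false claim of benefit.

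**Conclusion.** The concern holds in a limited form. The March to July part of the absenteeism count falls after the wait-list arm has been offered MBSR, so it does not compare MBSR with no intervention. September to March does.

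Dilution follows if controls take up the course and it lowers absence before July. Its size cannot be derived from the documents. At full uptake the illustration gives a loss of about 22-36% of the full-year log effect from the delayed course alone, and at 50% uptake about 11-17%. The additive version at full uptake gives 12-45%. These rest on the assumed calendar throughout and, on the ratio scale, also on the assumed absence ratio of 0.70.

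Absenteeism is one of four secondary aims. Perceived stress, the other questionnaire outcomes and the sample size are untouched. This is a moderate issue that should be settled before analysis. It does not threaten the trial's main conclusion.

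**What to change.** Define the between-arm absenteeism outcome as days and spells absent from the September start of the programme to the March follow-up, ending before the first control-arm session. Adjust for prior-year absence.

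A November to March count can be added as supportive. Report the full-year total descriptively, or label it as early versus delayed MBSR. The choice of count model can stay with the analysis plan.

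**Cost.** A change of wording, plus extraction of dated absences from the teachers' own records or the schools' absence system already used for verification. No new visit is needed. This depends on the entries carrying dates, which the protocol does not state, so it should be confirmed first. The price is a shorter window with fewer absence days, and therefore less precision. The change restores the stated comparator and does not promise more power.
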